## Methods

### Design

An RCT will be conducted to compare the IG (Paivina-Care) with a WCG. Self-reported assessments will take place at baseline (T1), peritreatment (after completion of Session 5, T2 in IG), posttreatment (after completion of Session 8 or 12 weeks after randomization, T3) and at a 6-month follow-up (T4; see Figure 1 for a detailed overview). Self-reported data will be collected using a secure online-based assessment system (AES, 256-bit encrypted). All procedures involved in the study will be consistent with the generally accepted standards of ethical practice. The study was approved by the Friedrich-Alexander University Erlangen-Nürnberg ethics committee (no. 324_15B). The trial is registered in the German clinical trials register under DRKS00010228. All participants gave written informed consent in accordance with the Declaration of Helsinki.

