**Method:**

Two hundred women who meet the criteria for GPPPD and have not been able to experience sexual intercourse for at least the last 6 months will be recruited and randomly assigned either to the intervention group (IG) or a 6-month waitlist control group. Assessments take place at baseline (T1), peritreatment after completion of Session 5 in IG (T2), after completion of Session 8 or 12 weeks after randomization (T3), and after 6 months (T4). Data will be analyzed on an intention-to-treat and a completer basis.

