#### Stepwise Procedure: Assessment of Eligibility and Randomization

Women who sign up as potential participants will receive an online information letter with detailed information on the study procedures. They will be asked to provide an email address that they want to use for the study and a first and last name (which can be pseudonyms if desired). The women will be informed that they can withdraw from the intervention and/or study at any time without any negative consequences. Applicants who intend to participate in the study will be asked to complete online screening questionnaires that assess inclusion and exclusion criteria. If responses to this questionnaire indicate that participants might be affected by one of the mental health disorders listed as exclusion criteria above, participants will be scheduled for the SCID-I *via* telephone. Women who meet all of the inclusion criteria and none of the exclusion criteria and who complete the baseline assessment and return the informed consent form will be considered for the study and randomly allocated to one of the two study conditions. Randomization will take place at an individual level. This process will be completed by an independent researcher not otherwise involved in the study using an automated computer-based random integer generator (randlist). Until this process has been completed, the results will not be known by participants, researchers involved in recruitment or eCoaches. Participants will be informed of the outcome of the randomization, and participants in the IG will receive immediate access to the program. Participants in the WCG will receive access to the program 6 months after study intake.

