### Intervention

The intervention consists of eight sessions composed of modules for psychoeducation (Sessions 1–2), cognitive restructuring (Session 2), non-judgmental awareness (Session 2), relaxation exercises (Session 3), attention-focusing for pain-management (Session 3), body exposure and genital self-exploration (Session 4), gradual exposure with fingers (Session 3) and with dilators (Sessions 5–6), sensate focus (Sessions 5–6), preparation exercises for sexual intercourse (Session 7), and relapse prevention (Session 8). A booster session is provided four weeks after the end of the program (Session 9) (see Table 1 for a session overview). The intervention builds on elements of an evaluated cognitive-behavioral intervention for women with vaginismus and the treatment manual for the present intervention (67, 68). Each session can be completed in approximately 45–60 min. We advise participants to do at least one and no more than two sessions per week. Participants can, however, take more time for session completion if needed. Consequently, the intervention lasts about 8–16 weeks (plus a booster session). Lessons consist of general text-based information including a discussion of the rationale for each program component, testimonials as well as interactive elements such as exercises (all sessions), quizzes (Session 1), mp3 audio files (Session 3), video clips (Sessions 1 and 3), and downloadable worksheets (Sessions 1, 3, 4, 5, and 7). The program is adaptive, as the content is tailored to the specific needs of the individual participant by continuously asking participants to choose among various response options. Subsequent content is then tailored to each participant’s response. Participants will have the possibility to rate how useful they find the modules, how easy the modules are understood, how long they take to complete them, and to add additional comments and feedback. Using responsive web-design, participants can follow the program on a computer, tablet, or mobile phone. Participants can also use an integrated read-aloud function to listen to the texts. Difficulties with exercises as well as challenges, obstacles, disappointment, and setbacks that may occur in the course of treatment are addressed in several sessions. Participants are encouraged to keep a daily online training diary to monitor exacerbating and alleviating factors regarding the use of the different techniques in the program. One key feature of the intervention is the focus on transfer tasks (homework assignments), which allow participants to integrate newly acquired strategies and techniques into daily life.

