### Primary and Secondary Outcomes

Primary outcome will be sexual intercourse at posttreatment. In secondary analyses, the effects of the intervention, e.g., on nonintercourse penetration behavior, fear of sexuality, sexual functioning, and cognitions regarding vaginal penetration, will be examined.

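### The primary time point T3 has two triggers and no rule for choosing between them, so intervention women can be assessed at a different time after randomization from waitlist women

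*Protocol article*

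**What the plan says.** The Design section of the protocol article places the primary assessment at "posttreatment (after completion of Session 8 or 12 weeks after randomization, T3". The abstract repeats the two triggers: "peritreatment after completion of Session 5 in IG (T2), after completion of Session 8 or 12 weeks after randomization (T3), and after 6 months (T4". There the intervention group is named for T2 only. Neither place assigns a T3 trigger to an arm or says which date counts when they differ. The outcome section ties the primary endpoint to this visit: "Primary outcome will be sexual intercourse at posttreatment". The sample size section does the same.

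Three other statements bear on the timing:

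- Waitlist access: "Participants in the WCG will receive access to the program 6 months after study intake".
- Pace and length, in the Intervention section: "We advise participants to do at least one and no more than two sessions per week", then "Participants can, however, take more time for session completion if needed", then "Consequently, the intervention lasts about 8–16 weeks (plus a booster session".
- Order of content, in the same section: "preparation exercises for sexual intercourse (Session 7".

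The Design section refers to Figure 1 for detail. That figure is not available here, and its absence is not counted against the plan.

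**The concern.** One trigger is a calendar date and the other is something the participant does after randomization. Only the intervention arm can do it before T3. If the Session 8 trigger operates at all, time since randomization at the primary assessment depends on adherence in one arm and is fixed in the other. A woman assessed earlier has had less time to succeed and a woman assessed later has had more, whether or not the programme works. The primary chi-square comparison would then mix the effect of the programme with unequal follow-up.

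A separate matter is what T3 measures. If week 12 also applies to intervention women, those on a slow course are assessed before they finish, and possibly before the session on intercourse. The label *posttreatment* would not fit them.

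**Working it through.** **1. The plan's own figure.** Inputs from the sample size section: w = 0.20, 80% power, two-tailed alpha 0.05, 200 women. With a chi-square test on 1 df and noncentrality N × w², the smallest N giving 80% power is 197 (power 0.802). N = 200 gives 0.807. The stated 200 is reproduced. The calculation contains no time input, so the timing of T3 does not alter it.

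**2. Which trigger can apply to the waitlist.** Programme access opens after 6 months, so no waitlist woman can complete Session 8 before T3. Her T3 is week 12.

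**3. When intervention women are assessed.** Assume an even pace, so weeks per session = course length ÷ 8.

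| Course length | Session 6 done | Session 7 done | Session 8 done |
|---|---|---|---|
| 8 weeks | week 6 | week 7 | week 8 |
| 12 weeks | week 9 | week 10.5 | week 12 |
| 16 weeks | week 12 | week 14 | week 16 |

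| Reading of *or* | Intervention T3 | Waitlist T3 | Can T3 precede Session 7? |
|---|---|---|---|
| Session 8 governs the intervention arm | weeks 8–16 | week 12 | no |
| Earlier date counts | weeks 8–12 | week 12 | yes, on slow courses |
| Later date counts | weeks 12–16 | week 12 | no |

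Under the earlier-date reading, Session 7 is unfinished at week 12 on any course longer than 12 × 8/7 = 13.7 weeks. On a 16-week course, 6 of 8 sessions are done by then.

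**4. Size of a pure timing effect (illustration).** Assumptions: no treatment effect; success accrues at a constant rate and persists; the rate reaches p₁₂ by week 12; 100 women per arm (the allocation ratio is not stated). The article gives no background rate, so p₁₂ is varied from 5% to 30%. The rate at week t is p(t) = 1 − (1 − p₁₂)^(t/12). The target difference comes from solving w = (p_I − p_W) / (2√(p̄(1 − p̄))) = 0.20, where p̄ is the mean of the two rates.

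| p₁₂ | Rate at week 8 | Difference, points (rejection probability) | Rate at week 16 | Difference, points (rejection probability) | Target difference at w = 0.20, points |
|---|---|---|---|---|---|
| 5% | 3.36% | −1.6 (0.09) | 6.61% | +1.6 (0.08) | 12.7 |
| 10% | 6.78% | −3.2 (0.13) | 13.11% | +3.1 (0.11) | 15.2 |
| 20% | 13.82% | −6.2 (0.21) | 25.73% | +5.7 (0.16) | 18.2 |
| 30% | 21.16% | −8.8 (0.30) | 37.85% | +7.8 (0.22) | 19.6 |

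The last week-16 entry is 1 − 0.7^(16/12) − 0.30 = 0.0785 (0.07847 before rounding). Rejection probabilities compare with a nominal 0.05. Each row places every intervention woman at the same extreme, so real effects would be smaller.

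**5. The separate matter of incomplete treatment (illustration).** Suppose 10% of intervention women are read before Session 7 and have the waitlist success rate, with that rate at 5–20%. Power then falls from 0.81 to about 0.73–0.75. With 30% it falls to about 0.53–0.58. A common assessment date does not remove this effect.

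**6. Pace against stated length.** Eight sessions at one to two per week take 8 ÷ 2 = 4 to 8 ÷ 1 = 8 weeks, against the stated 8 to 16. The allowance for extra time accounts for an upper end beyond 8 weeks. It does not account for a lower end of 8 rather than 4.

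**The case against.** The strongest reply is that this is loose wording in a condensed article. The full protocol or Figure 1 may state the rule, and exact invitation dates are the kind of detail an article leaves out. That stands as far as the missing rule goes. It does not settle the timing: as long as the Session 8 trigger in the text is used, some intervention women are read at a time other than week 12. A figure could cure this only by dropping that trigger.

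The size is also open to challenge, fairly. Entrants have had no intercourse for at least 6 months, so background success may be at or below the low end of the range. Early and late readings partly cancel. The model treats success as cumulative. The article gives a two-week recall period under the six non-intercourse items. If that period also covers the intercourse item, the outcome is recent status and the model does not fit.

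Several stronger readings are tempting, but the article does not support them:

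- That Session 8 is the rule for the intervention arm. The waitlist half follows from the access date; the intervention half is one reading of an unresolved *or*.
- That T3 both waits for Session 8 and falls before Session 7. It can precede Session 7 only if week 12 caps the intervention arm, and those women are then read at the same time as the waitlist.
- That the timing effect has a known direction. An earlier-date rule can only work against the intervention; a later-date rule can only favour it.
- That T3 could fall at week 4. This needs the fastest advised pace, which the stated 8 to 16 weeks excludes.
- That waitlist women have access before T4. The abstract pairs a 6-month waitlist with assessment after 6 months, and nothing shows that the two dates differ.

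**Conclusion.** The point holds as an ambiguity in the primary time point that allows adherence-dependent, unequal follow-up. Every reading that keeps the Session 8 trigger gives some intervention women a different time since randomization from the waitlist. The possible distortion at the extremes is about −1.6 to −8.8 points (all at week 8) or +1.6 to +7.8 points (all at week 16), given constant accrual and an assumed background of 5–30% by week 12. In practice it would probably be smaller, and the documents do not allow a closer estimate. The planned 200 stands. This is a cheap improvement to the plan and does not show that the comparison is invalid.

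**What to change.** Define the primary T3 as 12 weeks after randomization in both arms, with the same response window, regardless of sessions completed. Week 12 is already in the plan. A questionnaire triggered by Session 8 can stay as process data only.

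Describe the primary estimate as the effect at 12 weeks after randomization and not as posttreatment, since women on a 16-week course will have done about 6 of 8 sessions and not Session 7 by then. The change equalizes timing; it does not make treatment complete for slow participants.

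The Intervention section's advised pace and its stated programme length must also be reconciled.

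The cost is a wording change and a reprogrammed invitation date. Fast completers would answer some weeks after finishing, which adds some risk of dropout, and the article itself notes that women who succeed before completing treatment tend to leave the study. The telephone assessment and eCoach reporting already planned for the primary outcome partly cover this. The sample size needs no change.

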**Figure 1 F1:**
[figure not shown]
Flow of participants.

### Participants and Procedure

#### Inclusion and Exclusion Criteria

We will include women who (1) have not been able to have sexual intercourse in at least the last 6 months conformed to DSM-5, as indicated by scores ≤ 1 on Primary Endpoint Questionnaire (PEQ) item 7 (60), (2) are at least 18 years of age, (3) whose penetration difficulties are not due to a medical condition, (4) are in a heterosexual relationship or have a heterosexual (training) partner, (5) who have Internet access, (6) have sufficient German skills in reading and writing, and (7) are willing to give informed consent.

We will exclude individuals reporting to have been diagnosed with (1) psychosis or dissociative symptoms in the past or present, (2) posttraumatic stress disorder or traumatization due to sexual abuse in the past or the present, (3) substance abuse or dependency in the present, or (4) moderate or severe depression or bipolar disorder in the present assessed with the Structured Clinical Interview for Diagnostic and Statistical Manual of Mental Disorders (fourth edition) Axis I Disorders (SCID-I) (66), and those (5) currently being treated for GPPPD.

#### Recruitment

We will recruit patients *via* (1) the study website and Facebook page, (2) articles in women’s online magazines, (3) online forums, (4) advertisements on websites related to the topic of sexual dysfunctions, and (5) Google AdWords. Recruitment is scheduled to take place between April 2016 and December 2017. The trial is open to all women fulfilling the inclusion criteria. The research website www.paivina-care.info provides information on the program and details about the study. If they want to participate in the study, applicants can sign up on this website by leaving their email address.

#### Stepwise Procedure: Assessment of Eligibility and Randomization

Women who sign up as potential participants will receive an online information letter with detailed information on the study procedures. They will be asked to provide an email address that they want to use for the study and a first and last name (which can be pseudonyms if desired). The women will be informed that they can withdraw from the intervention and/or study at any time without any negative consequences. Applicants who intend to participate in the study will be asked to complete online screening questionnaires that assess inclusion and exclusion criteria. If responses to this questionnaire indicate that participants might be affected by one of the mental health disorders listed as exclusion criteria above, participants will be scheduled for the SCID-I *via* telephone. Women who meet all of the inclusion criteria and none of the exclusion criteria and who complete the baseline assessment and return the informed consent form will be considered for the study and randomly allocated to one of the two study conditions. Randomization will take place at an individual level. This process will be completed by an independent researcher not otherwise involved in the study using an automated computer-based random integer generator (randlist). Until this process has been completed, the results will not be known by participants, researchers involved in recruitment or eCoaches. Participants will be informed of the outcome of the randomization, and participants in the IG will receive immediate access to the program. Participants in the WCG will receive access to the program 6 months after study intake.

### Intervention

The intervention consists of eight sessions composed of modules for psychoeducation (Sessions 1–2), cognitive restructuring (Session 2), non-judgmental awareness (Session 2), relaxation exercises (Session 3), attention-focusing for pain-management (Session 3), body exposure and genital self-exploration (Session 4), gradual exposure with fingers (Session 3) and with dilators (Sessions 5–6), sensate focus (Sessions 5–6), preparation exercises for sexual intercourse (Session 7), and relapse prevention (Session 8). A booster session is provided four weeks after the end of the program (Session 9) (see Table 1 for a session overview). The intervention builds on elements of an evaluated cognitive-behavioral intervention for women with vaginismus and the treatment manual for the present intervention (67, 68). Each session can be completed in approximately 45–60 min. We advise participants to do at least one and no more than two sessions per week. Participants can, however, take more time for session completion if needed. Consequently, the intervention lasts about 8–16 weeks (plus a booster session). Lessons consist of general text-based information including a discussion of the rationale for each program component, testimonials as well as interactive elements such as exercises (all sessions), quizzes (Session 1), mp3 audio files (Session 3), video clips (Sessions 1 and 3), and downloadable worksheets (Sessions 1, 3, 4, 5, and 7). The program is adaptive, as the content is tailored to the specific needs of the individual participant by continuously asking participants to choose among various response options. Subsequent content is then tailored to each participant’s response. Participants will have the possibility to rate how useful they find the modules, how easy the modules are understood, how long they take to complete them, and to add additional comments and feedback. Using responsive web-design, participants can follow the program on a computer, tablet, or mobile phone. Participants can also use an integrated read-aloud function to listen to the texts. Difficulties with exercises as well as challenges, obstacles, disappointment, and setbacks that may occur in the course of treatment are addressed in several sessions. Participants are encouraged to keep a daily online training diary to monitor exacerbating and alleviating factors regarding the use of the different techniques in the program. One key feature of the intervention is the focus on transfer tasks (homework assignments), which allow participants to integrate newly acquired strategies and techniques into daily life.

**Table 1 T1:** Content of the GPPPD program.

Intervention content	Session
Psychoeducation I	1
Psychoeducation II, cognitive restructuring, and non-judgmental awareness	2
Muscle and breathing relaxation, pelvic floor relaxation, attention-focusing for pain management, and gradual vaginal exposure with fingers	3
Body exposure and genital self-exploration	4
Gradual vaginal exposure with dilators I and sensate focus I	5
Gradual vaginal exposure with dilators II, sensate focus II, and building sexual desire and arousal	6
Sexual intercourse	7
Plan for the future, relapse prevention	8
Booster session	9

Internet-based interventions have the advantage of directly promoting health behavior change in the daily life of participants, who are supported and encouraged to complete exercises such as progressive muscle relaxation (PMR) and dilator insertion. In each session, participants are introduced to a new or a follow-up strategy which then has to be practiced in everyday life. The use and implementation of the transfer tasks is then reviewed at the beginning of each session and participants are encouraged to continue exercising each task throughout the intervention. The implementation of the transfer tasks is also supported by text messages on the smartphone including motivational messages and practice reminders. These messages are meant to encourage participants to apply what they have learned in their daily lives. If desired, participants will receive one text message every day during an 8-week period.

The secure web-based platform (AES 256-bit encryption) mentioned above will also be used for the intervention and the communication between participants and eCoaches. Participants will access the platform using their email address and chosen password.

#### Psychoeducation (Sessions 1–2)

The participants will be provided with psychoeducational information on GPPPD and the multifactorial causes of its development. Core elements in the first session are (1) overview of the program: intervention components and the expectations placed on the participants are presented; (2) goal setting: participants are asked to define realistic individual treatment goals, which will be shown and can be modified over the course of the program; (3) strengthening motivation: personal treatment motivation is assessed, participants can schedule the exercises and plan how to deal with difficulties they may face during treatment, for example non-adherence to treatment and exercises; (4) self-support: participants learn about effective support, e.g., in terms of self-gratification; (5) couples’ communication: rules for communication are introduced to facilitate the discussion between participants and their partners about the intervention and the partner’s role in the program, especially with regard to exercises, the expression of emotional needs, and sexual preferences.

In the second part of psychoeducation (Session 2), participants will be introduced to the fear-avoidance model and thereby learn more about the causal and maintaining factors of GPPPD and the rationale behind the treatment. Participants are given the opportunity to individualize their own fear-avoidance model by including their cognitions, emotions, physical reactions, and behaviors. Participants also learn about the function of emotions and their influence on GPPPD symptoms.

